## Abstract

**Background:**

Axial spondyloarthritis (axSpA) is a disabling inflammatory joint disease with chronic low back pain (CLBP) as leading symptom. Recognizing axSpA in the large amount of CLBP patients is difficult for general practioners (GP). This evaluation aims to assess the effect of a referral strategy for axSpA in young primary care patients with CLBP by comparing the use of the strategy with usual care. The effect is measured at three different levels; by patient reported outcomes (the clinical effect), process and costs evaluation.

**Methods/Design:**

This study design is a cluster randomized controlled trial with GP as clusters. GPs throughout the Netherlands are invited to participate and randomized to either the intervention or the control group. Patients from participating GPs are invited to participate if they have ever been registered with low back pain, without radiation (ICPC L03) and aged 18–45 years. To be included in the study, patients need to have current low back pain and chronic low back pain (>12 weeks). In the intervention arm a referral strategy for axSpA will be applied in CLBP patients, in the control arm care as usual will be provided for CLBP patients. The referral strategy consists of four easy to use variables. All are questions about the back pain complaints of the patients. Data is prospectively collected in an online database at baseline (T0), 4 months (T1), 12 months (T2) and 24 months (T3). After time point T1 (4 months) patients from the control group will also receive the intervention i.e. the application of a referral strategy for axSpA. The effect of the referral strategy is measured at three different levels, by patient outcomes (e.g. pain scores, quality of life), process measures (e.g. number of axSpA diagnoses by rheumatologists) and by costs (work productivity and health care resources use). Our primary outcome is the Roland Morris Disability Questionnaire after 4 months, secondary outcomes are pain and quality of life. Costs will be assessed before and after the use of the referral strategy, to estimate if the use of the strategy will lead to a reduction in health care costs and improvement in work participation.

**Discussion:**

It is anticipated that using the axSpA referral strategy for primary care CLBP patients will increase the quality of life of CLBP patients, will result in more (correct) diagnoses of axSpA by the rheumatologists, and will be cost-effective. Ultimately, the results of this study may contribute to the startup of a national implementation of the axSpA referral strategy to identify timely CLBP patients with axSpA.

**Trial registration:**

NCT01944163, date of registration; September 6, 2013 (Clinicaltrials.gov)

## Background

Low back pain (LBP) is one of the most common musculoskeletal disorders affecting up to 85 % of the adults at some point in their lives [1]. In 10–28 % of the patients the pain persists for more than 12 weeks and becomes chronic [2]. On top of the high prevalence, LBP is the leading cause of years lived with disability (YLD). The YLD of low back pain is higher than the YLD of e.g. major depressive disorders, anemia, chronic obstructive pulmonary disease and diabetes [3].

One of the possible causes of chronic low back pain (CLBP) is axial spondyloarthritis (axSpA) which is a heterogeneous inflammatory joint disease. Two recent studies showed a prevalence of axSpA among young (18–45 years) CLBP patients between 16 % and 24 % [4, 5]. Recently the focus of axSpA is on early diagnosis considering treatment is more effective in patients with short symptom duration [6]. For an early diagnosis of axSpA by rheumatologists, early recognition in primary care is important. However recognition of axSpA is difficult because specific signs or symptoms do not exist [7]. Moreover, in the current CLBP guidelines for GPs no referral guidelines for axSpA are included [8].

Within the field of rheumatology several models to identify patients at high risk for axSpA have been published, these models combine multiple predictors, such as clinical symptoms, patients’ characteristics and test results to estimate the probability of the disease. Almost all published referral models are tested in a pre-selected population with a high prior probability of axSpA. Only one referral strategy is developed and externally validated in a primary care CLBP population, the CaFaSpA referral rule [4, 5]. This low cost referral rule is easy to use and consists of four variables, all variables are questions. The GP can ask these questions while taking a patient’s history.

After development and external validation of a referral rule the next step before application in daily practice is to investigate the impact of the referral rule [9, 10]. Since the CaFaSpA referral rule can identify axSpA patients, it is worthwhile to perform an impact analysis to determine its effect in primary care.

### Objective of the evaluation

This study entails a clinical effect, process and cost evaluation of using the axSpA referral strategy for primary care CLBP patients. The study aims to determine to what extent use of the rule, in comparison with usual care, leads to less disability and pain and improved quality of life in CLBP patients. Second, it evaluates if the referral strategy leads to more diagnosis of axSpA and finally health care costs and work participation will be compared before and after the application of the referral strategy.

## Methods

### Design

The study uses a cluster randomized controlled trial design which is carried out in the primary care setting in the Netherlands. Sixty primary care practices will be randomized to either the intervention or the control (usual care) group. Each cluster contains the GPs from one practice and their included patients.

### General practices

GPs at the surrounding areas of participating Dutch rheumatologists will be invited to participate by an invitation letter. Two weeks after this invitation letter a member our research team will call the GP to assure if the GP was interested in participating. The only exclusion criteria for GPs is not using the International Classification of Primary Care (ICPC) coding system for their patients, as patients will be selected from the GP practice using the ICPC system. The ICPC is the standard for coding and classification of signs, symptoms and complaints in general practice. The Dutch ICPC is managed and maintained by the Netherlands Society of General Medical Practitioners (NHG). At present, most general practice information systems use the ICPC codes.

### Recruitment of patients and eligibility criteria

Patients will be recruited from participating practices by searching their records for patients with ICPC L03 and aged between 18 and 45 years. The recruitment of patients is the same for GPs randomized to the intervention as for GPs randomized to the control group. All selected patients will receive a letter from their GP briefly explaining the study and asking the patient to respond using the attached return form. If the patient does not respond to the invitation within 4 weeks, a second invitation letter will be sent.

The inclusion criteria are:Age 18–45 yearsEver registered with low back pain, without radiation ICPC L03Current low back pain≥12 weeks low back pain

The exclusion criteria are:A clear explanation for the back pain (like a trauma, hernia nuclei pulposi or malignancy)Mentally incompetent (inability of a person to make or carry out important decisions regarding his or her affairs)No understanding of the Dutch language (written)

Patients who agree to participate sign a consent form, thereafter they will be called by a research assistant to confirm the inclusion criteria. The research assistant will register the answers to the CaFaSpA referral rule of the participant. After this telephone contact the patient will receive online questionnaires per email concerning their back pain. If email contact it is not possible, the patient will receive the questionnaires by post.

Those who do not wish to participate will be registered by gender, date of birth and the reason for not participating, such as no current low back pain, no time, etc.

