### Intervention

The intervention is the application of the CaFaSpA referral rule by GPs in young primary care patients with CLBP [4]. [5] (Table 1) The CaFaSpA rule is explained to GPs, first by phone and thereafter by sending written materials explaining the referral rule. To ensure that the intervention is equally applied in all participants, not the GP but a research assistant registers the answers to the referral rule from a patient. This takes place in the same telephone contact in which the inclusion and exclusion criteria are checked. The outcome of the intervention i.e. the outcome of the CaFaSpA referral rule is communicated by a letter to both the GP and the participant. If the referral rule is positive, a referral to the rheumatologist will be advised. Thereafter it is the responsibility of the GP and the patient to arrange a referral to the rheumatologist.

**Table 1 Tab1:** The CaFaspA referral strategy

Applicable in patients ≥3 months back pain and age at oneset <45 years
*Inflammatory back pain*
Inflammatory back pain is considered present if at least four questions are answered with yes
-Age at onset<40 years
-Insidious onset
-Improvement with exercise
-No improvement with rest
-Pain at night (with improvement upon getting up)
*Positive family history*
A positive family history is considered present if there is a first or second degree family member with axial spondyloarthritis, Crohn’s disease, psoriasis or uveitis anterior
*Good reaction to NSAIDs*
*A* good reaction to NSAIDs is present when a patient reports a relieve in pain perception within 48 hours after receiving a NSAID
*CLBP ≥5 years*
A long low back duration is present if the duration of the back pain is 5 years or longer
If at least two out of the four referral parameters are present → a referral to the rheumatologist is advised

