### Control group

Participating patients of the control group are also called by our research assistant to check the inclusion criteria and to register the answers to the CaFaSpA referral rule. No active advice regarding a referral takes place. If control group patients choose to go to their GP, they will be treated according to the Dutch College of General Practice guidelines for the management of low back pain [11].

Before the IMPACT study started we discussed with GPs the weaknesses and difficulties of our study design. We received feedback concerning the benefit of participating for GPs or patients who were randomized to the control group. It was feared that the lost to follow up would be great in the usual care group. To increase the feasibility of our study we decided to communicate the outcome of the referral rule to the control group after 4 months and thereby eliminating the contrast between the intervention and usual care group.

Therefore, four months after inclusion (after our primary outcome time point) the usual care CLBP patients and their GPs will receive a letter containing the outcome of the referral rule and an advice to refer or not refer the patient. After receiving the outcome of the referral rule the patients of the control group will be followed for two years, data will be collected after 1 and 2 years of exposure to the referral rule, this will be sixteen and twenty-eight months after inclusion of the study (Fig. 1).

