### Data collection

Data collection of patient outcomes are at baseline (T0) (directly after inclusion of a patient in the study), after 4 months (T1), after 12 or 16 months (T3) and after 24 or 28 months (T4) (Fig. 1). At each time point patients will automatically receive an email with a link to online questionnaires.

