### Compliance

The compliance of patients is optimized by sending up to three reminders emails, asking the patient to fill out the online questionnaires. If the patient still has not completed the questionnaires the research assistant will contact the patient by telephone and the questionnaires are sent to the patient by post.

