A weakness of the study is that the contrast between intervention and control groups disappears after 4 months, as patients of the control group are also provided with the advice of the referral strategy. Nevertheless our primary outcome is assessed before the contract between intervention and control group is eliminated. We expect that 4 months is a sufficient period to achieve a substantial improvement in the primary outcome by using the referral strategy in the intervention group. For other outcomes we can use a before after design within patients which is acceptable as the back pain complaints are chronic. Another potential weakness is that patients are selected by a registry, rather than only actively care seeking patients are invited to participate. This can lead to a lower participation rate of the invited patients and a potential selection bias of only severe cases of low back pain. However in the prior CaFaSpA studies, the same approach to select participants by the GP register was conducted and this didn’t result in a more severe low back pain study population [4, 5]. In both CaFaSpA studies was the VAS pain comparable with other low back pain cohorts. One last limitation of this study is that the intervention i.e. the CaFaSpA referral rule is applied by research assistant not by GPs themselves, this pragmatic approach can influence the outcomes of the study. We have chosen for this pragmatic approach as GPs pointed before the start of study that it is often too busy during consultation hour to properly ask the questions of the referral rule and that the application of the referral rule would not be uniform but heavenly time dependent.

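### The control-arm result letter falls due by calendar at the same time as the T1 questionnaire, so late primary-outcome forms can be completed after the referral advice

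*Protocol article*

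**What the plan says.** Five sections of the protocol article bear on the order of questionnaires and letters.

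- **Recruitment:** the research assistant records the rule answers in the call that confirms eligibility. "After this telephone contact the patient will receive online questionnaires per email concerning their back pain".
- **Intervention:** in the intervention arm, "the outcome of the CaFaSpA referral rule is communicated by a letter to both the GP and the participant". No dispatch date is given.
- **Control group:** "four months after inclusion (after our primary outcome time point) the usual care CLBP patients and their GPs will receive a letter".
- **Data collection:** T0 is placed directly after inclusion and T1 at 4 months. The email with the questionnaire link goes out automatically at each time point.
- **Compliance:** non-responders are pursued by "sending up to three reminders emails". After that, "the research assistant will contact the patient by telephone and the questionnaires are sent to the patient by post". No closing window is stated.

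The Discussion concedes that the contrast disappears after 4 months and then offers this defence: "Nevertheless our primary outcome is assessed before the contract between intervention and control group is eliminated" (the fourth-last noun group evidently means contrast, not contract). The Randomisation section states that outcomes are self-reported and unblinded.

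**The concern.** The 4-month comparison is the only randomised contrast between advice and no advice, because the control arm receives the same advice afterwards. Its integrity depends on control patients answering T1 before they are told their result. The stated schedule fixes when the T1 form is sent and when the letter goes out. It does not link the letter to the form being completed.

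The exposure is one-sided by arm. At T1 only control patients can newly learn their result. At T0 only intervention patients can. In each arm the measurement at risk is the last one planned before exposure, which is also the natural 'before' point for the before-after comparisons described in Data analysis and Discussion. The Control group section itself reports a fear of heavy loss to follow-up under usual care, so slow response in that arm was foreseeable.

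**Working it through.** **1. Order of events at 4 months**

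| Event, control arm | Trigger | Section |
|---|---|---|
| T1 email | 4 months | Data collection |
| Result letter to patient and GP | 4 months after inclusion, described as after the primary time point | Control group |
| Up to three reminders, then telephone and post | Form still missing | Compliance |

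The first two events fall due at nominally the same time, and the third can only come later. A form obtained by chasing can therefore follow the letter. The intended order (T1, then letter) is stated, but only by calendar.

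**2. Order of events at baseline**

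The call comes first and the T0 email follows it. The intervention letter also reports a result obtained in that call. Nothing stated makes the letter wait for T0, but nothing says that it is sent promptly either.

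**3. What each gap can reach**

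The primary model in Data analysis has allocation, rule result, their interaction and a random intercept for practice. The outcome is the 4-month RMDQ, and baseline RMDQ is not a listed covariate. A T0 form completed after the letter therefore does not enter the primary estimate. A late control T1 form does.

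**4. The plan's own sample size**

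Inputs (Sample size section): difference 2.5, SD 6.0, two-sided alpha 0.05, power 0.80, 50% rule-positive, ICC 0.05, cluster size 16, 25% loss.

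- Per arm: 2 × (6.0 × (1.960 + 0.842) / 2.5)² = 90.4, so 91 per arm or 182 in total. The stated 180 matches the two-arm total, not a per-group number.
- 180 / 0.5 = 360.
- Design effect: 1 + (16 − 1) × 0.05 = 1.75, and 360 × 1.75 = 630.
- 630 / 0.75 = 840, as stated.

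After allowing for clustering and loss, this amounts to 90 rule-positive patients per arm. The power for 2.5 points is then 79.8%.

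**5. Dilution from late control T1 forms**

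Let f be the share of control T1 forms completed after the letter, and g the share of the full effect reached by then. Both are assumptions, because the document gives neither.

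Expected difference = 2.5 × (1 − f × g). Power is computed with 90 per arm and SD 6.0.

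| f | g | Difference | Loss | Power |
|---|---|---|---|---|
| 0 | – | 2.500 | 0 | 79.8% |
| 0.10 | 0.10 | 2.475 | 0.025 | 79.0% |
| 0.20 | 0.25 | 2.375 | 0.125 | 75.7% |
| 0.30 | 0.50 | 2.125 | 0.375 | 66.1% |

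The loss is 1% (0.025 / 2.5) to 15% (0.375 / 2.5) of the target difference. The table covers dilution only. A change in how patients answer once they know the result is also possible, but its sign and size are unknown.

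**The case against.** The strongest reply is that the article does set the order at T1. The Control group section places the letter after the primary time point, and the Discussion repeats the assurance. That stands: a reader might infer that the questionnaires are not sequenced at all, and for T1 the text does not support this. What remains is that the order is kept by calendar and not by receipt, while the Compliance section lets collection run on.

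Second, the baseline half rests on silence. The Intervention section gives no letter date, and a letter held until T0 is returned would fit the text. Letter logistics may well be in the full protocol. This also stands, and it is why the baseline half carries less weight.

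Third, the effect at T1 is probably small and conservative. After the letter, the patient and GP must still arrange a referral, so a slightly late form can reflect little change in care. Such dilution shrinks the difference and does not create a false positive. This is fair, and it argues for values of g near the low end. It does not remove the possible reporting effect in an unblinded, self-reported outcome.

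Fourth, some remedies would do harm. Completing T0 by telephone would change the mode of administration for slow responders only. Dropping late T1 forms from the control arm alone would be a one-sided exclusion after randomisation. Neither is proposed here.

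**Conclusion.** The point holds as a cheap improvement. Under the stated schedule, control-arm T1 forms that need chasing can be completed after the patient knows the rule result, so the Discussion's assurance about the primary outcome is not secured. The most plausible consequence is a slight dilution of the 4-month contrast. Under the assumed ranges (10-30% late forms, 10-50% of the effect reached) the loss is 0.025 to 0.375 points of 2.5, with power between 79.0% and 66.1% against 79.8%. The lower end is the more credible, given the steps between letter and treatment.

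Two stronger conclusions might be inferred and are not supported. One is that forms are in fact completed after exposure and that the primary result is biased: the document gives no letter dates, response times or counts of late forms, so this is a possibility and not a finding of fact. The other is that a contaminated baseline distorts the primary estimate: baseline RMDQ is not in the specified model, so the reach of late T0 forms is limited to the baseline table, the before-after analyses and any baseline-adjusted analysis.

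**What to change.** - **T1:** open the questionnaire in both arms early enough that the reminder cycle ends before the control letter is due. Alternatively, release the control letter on return of T1 or at the close of a stated window, whichever comes first.
- **T0:** obtain the self-completed form before the intervention letter is issued. The form can still be sent after the eligibility call.
- **Dates:** record the completion date of each form and the issue date of each letter.
- **Sensitivity analysis:** apply one completion cut-off, counted from inclusion, to T1 forms in both arms, so that the exclusion is symmetric.

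The sample size of 840 does not change. The cost is a revised email schedule or letter trigger and two recorded dates per time point. The downside is that T1 is measured slightly before 4 months, or that some letters go out slightly later. In the latter case the control arm's later assessments, which the Control group section counts as 1 and 2 years from exposure to the rule, should be timed from the recorded letter date.

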### Randomisation, allocation procedure and blinding

Primary care practices are randomly allocated to either the intervention or the control group. Randomisation is stratified for number of GPs working in the primary care practice (one or two vs more than two) to ensure similar number of patients in both groups. The block randomisation schedule is computer generated and administrated by an independent person, who is not involved in patient care. It is impossible to blind patients or GPs for allocation. If a patient receives the advice of a referral to the rheumatologist, both the patient and the GP are actively involved in this referral. Also the outcome assessment is not blinded, as patients assess the outcomes themselves by filling in questionnaires. Blinded analyses of the data will take place when possible.

### Intervention

The intervention is the application of the CaFaSpA referral rule by GPs in young primary care patients with CLBP [4]. [5] (Table 1) The CaFaSpA rule is explained to GPs, first by phone and thereafter by sending written materials explaining the referral rule. To ensure that the intervention is equally applied in all participants, not the GP but a research assistant registers the answers to the referral rule from a patient. This takes place in the same telephone contact in which the inclusion and exclusion criteria are checked. The outcome of the intervention i.e. the outcome of the CaFaSpA referral rule is communicated by a letter to both the GP and the participant. If the referral rule is positive, a referral to the rheumatologist will be advised. Thereafter it is the responsibility of the GP and the patient to arrange a referral to the rheumatologist.

**Table 1 Tab1:** The CaFaspA referral strategy

Applicable in patients ≥3 months back pain and age at oneset <45 years
*Inflammatory back pain*
Inflammatory back pain is considered present if at least four questions are answered with yes
-Age at onset<40 years
-Insidious onset
-Improvement with exercise
-No improvement with rest
-Pain at night (with improvement upon getting up)
*Positive family history*
A positive family history is considered present if there is a first or second degree family member with axial spondyloarthritis, Crohn’s disease, psoriasis or uveitis anterior
*Good reaction to NSAIDs*
*A* good reaction to NSAIDs is present when a patient reports a relieve in pain perception within 48 hours after receiving a NSAID
*CLBP ≥5 years*
A long low back duration is present if the duration of the back pain is 5 years or longer
If at least two out of the four referral parameters are present → a referral to the rheumatologist is advised

